### C) ANALYSIS

Two-tailed Fisher's exact tests and chi-squared tests will be used to compare proportions. Outcomes will be compared between groups in an intention-to-treat analysis without adjustment. Comparisons will be reported using relative risks (RRs) and numbers needed to treat (NNTs) along with their respective 95% confidence intervals (CIs).

*Post hoc* subgroup analyses will be performed on sex (female or male), age (<65 or ≥65 years), study site (Calgary or Kingston), procedural complexity (1-2 or 3-4), papilla status (native

papilla or prior sphincterotomy), disposition (inpatient or outpatient), biliary stent placement (present or none), and indication (suspected or confirmed malignancy or all others). All statistical analyses will be performed using RStudio version 1.2.1335 (Integrated Development Environment for R, Boston, USA).

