## **7.2. Secondary Outcomes**

The following will be recorded as secondary outcomes for the study:

- clinical success rate, defined as technical success rate in addition to a lack of repeat unplanned endoscopy, imaging, emergency department presentation, admission within 30 days of the index procedure for reasons related to ongoing pancreaticobiliary pathology that was initially thought to be resolved after the initial ERCP;
- subjective presence or absence of technical success as deemed by the endoscopist;
- assessment of overall ease of use of duodenoscope, using Likert scale of 1-10;
- procedure time;
- device failure or dislodgement rate of the disposable cap;
- overall adverse event rate (intraprocedural, early and late) and severity as defined and graded by the American Society for Gastrointestinal Endoscopy (ASGE) Lexicon within 30 days of the index procedure;
- pancreatitis rate, as defined by new or distinct abdominal pain after ERCP in addition to lipase rise above 3 times the upper limit of normal within 30 days of the index procedure;
- bleeding rate, as defined by hematemesis and/or melena and/or hematochezia, or drop in hemoglobin by  $\geq 2 \text{ g}^{23}$  following ERCP with either sphincterotomy or sphincteroplasty (or both) within 30 days of the index procedure;
- cholangitis and/or sepsis rate within 30 days of the index procedure;
- hospital admission or unplanned presentation to an acute healthcare facility within 30 days of the index procedure;
- mortality rate within 30 days of the index procedure;
- manual post-ERCP disinfection time (in endoscopy unit);
- reprocessing time (in automated reprocessing room).

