#### **D) OUTPUTS**

1. Table comparing proportions of variables between study groups
2. Summary of RRs, ARRs, RRRs, NNTs, NNHs
3. Subgroup analyses and forest plot of subgroups

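### Eight subgroup factors and a forest plot are planned with no interaction test, so uneven within-level significance could be read as a differing effect of the cap

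*Supplement*

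**What the plan says.** SAP section C gives one analysis rule for all outcomes: "Two-tailed Fisher's exact tests and chi-squared tests will be used to compare proportions", and "Outcomes will be compared between groups in an intention-to-treat analysis without adjustment". Results are relative risks and numbers needed to treat, "along with their respective 95% confidence intervals (CIs").

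The same section states that "subgroup analyses will be performed on sex (female or male), age" and six further factors: study site, procedural complexity, papilla status, disposition, biliary stent placement and indication. Each has two levels. The analyses are labelled post hoc. SAP section D lists "Subgroup analyses and forest plot of subgroups" among the outputs. Neither section names an interaction or homogeneity test, or says which outcome or outcomes the subgroups apply to.

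The later (two-centre) protocol, section 7.2, lists 13 secondary outcomes under "The following will be recorded as secondary outcomes for the study". It gives no order, multiplicity rule or exploratory label. Section 9.1 gives hypotheses, alpha and power for the two co-primaries only.

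**The concern.** A forest plot of 16 subgroup levels invites the reader to ask where the cap works and where it does not. The plan gives no tool for that question. What is left is to see which intervals exclude no effect, and that mostly reflects how many patients and events fall in each level. A cap that works equally well in everyone could be reported as working in one sex, one centre or one complexity band only. That could influence which patients or units are offered the device.

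The secondary outcomes raise a smaller version of the same issue. Relative risks and numbers needed to treat or harm would appear for outcomes on which the trial was not sized, with no statement of their standing.

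**Working it through.** **Inputs.** Contamination 10% v 3%, two-sided 5%, 80% power, 194 per arm (protocol 9.1). Microbiology N = 422, so 211 per arm; technical and secondary N = 518, so 259 per arm (SAP A). Technical success 92% (protocol 9.1). Eight two-level factors (SAP C). The protocol expects 25% of the sample from Kingston; no other level shares are given. Shares of 25% to 50% and independence between factors are therefore assumptions.

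**1. The plan's own figure.** With mean rate 0.065,
n = [1.96 √(2 × 0.065 × 0.935) + 0.842 √(0.10 × 0.90 + 0.03 × 0.97)]² / 0.07² = (0.683 + 0.290)² / 0.0049 ≈ 194 per arm.
This matches the protocol. The size is for the whole comparison and leaves little for halves or quarters of it.

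**2. Power within a level.** Exact power of two-sided Fisher at 10% v 3%:

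| Share of 211 per arm | n per arm | Power |
|---|---|---|
| 100% | 211 | 81% |
| 75% | 158 | 66% |
| 50% | 105 | 45% |
| 25% | 53 | 15% |

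**3. Discordance for one factor when the effect is identical in both levels.**
- 50/50 split: 2 × 0.45 × 0.55 = 0.50.
- 25/75 split: 0.15 × 0.34 + 0.66 × 0.85 = 0.05 + 0.56 = 0.61.

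Eight factors therefore give 8 × 0.50 = 4.0 to 8 × 0.61 = 4.9 discordant factors on average.

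**4. At least one discordant factor of eight.** The factors share the same events, so the figures in step 3 cannot be combined as if independent. Simulation with Fisher's test in each level and mixed shares of 25% to 50% gives about 93% of trials, with a mean of 4.2 to 4.3 factors. Setting every factor at 50/50 gives 89%; every factor at 25/75 gives 93%.

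**5. When there is no effect at all.** With technical success 92% v 92% and 259 per arm, about 30% of trials show at least one significant level. With contamination 5% v 5%, about 25% do.

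**6. What an interaction test achieves.** Eight independent tests at 5% give 1 − 0.95⁸ = 34%. Simulation with a simple risk-difference interaction test gives 27% to 35% for contamination under the uniform effect, and 30% to 33% for technical success with no difference. Misleading signals for contamination fall from about 93% to about 30%; for technical success there is no reduction. Over both co-primaries, 16 independent tests give 1 − 0.95¹⁶ = 56%.

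**7. Secondary outcomes.** Of the 13, "device failure or dislodgement rate of the disposable cap" applies to one arm only, leaving at most 12. If all 12 nulls are true and each is tested at 5%: 1 − 0.95¹² = 46% if independent, 32% at correlation 0.5, 18.5% at 0.8. At 259 per arm the true size of Fisher's test is 0.9% at a 1% event rate, 2.1% at 2% and 3.2% at 5%. With assumed rates for eight binary outcomes and 5% for four continuous ones, the independent figure falls to about 36%.

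**The case against.** The SAP calls the subgroups post hoc, which already marks them as not confirmatory. It prescribes relative risks and intervals, not p-values within levels, so reading significance off the plot is a foreseeable misuse and not a planned analysis. Nor is the 93% a false-positive rate for effects: it assumes a real, uniform effect and measures low power. All of this stands. It does not supply a way of judging whether effects differ, which is the purpose of the plot.

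It is also fair to object that interaction tests are no cure, since about 30% of trials would still show one by chance for each co-primary. That stands, and is why the tests must be labelled exploratory.

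On the secondary outcomes, a reader might infer that the SAP deliberately waives multiplicity control at a full 5% and that a spurious difference is likely. The documents do not support this. The phrase about adjustment most naturally means covariate adjustment. No alpha is stated for secondaries; 5% is only implied by the 95% intervals. SAP C names tests for proportions only. The SAP dictionary has no variable for several protocol secondaries, such as clinical success, endoscopist-judged success, admission or acute presentation, and the two cleaning times. The family-wise rate stays below one half even with 12 independent tests. The protocol also separates the co-primaries clearly by giving hypotheses and power to them alone.

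**Conclusion.** The concern holds for the subgroup analyses. The plan shows effects across eight factors without any test of whether they differ. If the contamination effect is uniform at the planned 10% v 3%, within-level significance would differ between levels for at least one factor in about 93% of trials (89% to 93% over the shares tried). This rests on independent factors, assumed shares and Fisher's test at 5% in each level.

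For the secondary outcomes the gap is one of wording. The family-wise rate is roughly 18% to 46% for up to 12 comparisons if all nulls are true, and lower where Fisher's test is applied to rare events.

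Biliary stent placement needs separate caution. It is decided during the procedure, after randomisation (protocol 8.1), and stenting itself can count as technical success for strictures and difficult stones (protocol Table 1). A subgroup effect on that factor is not a clean randomised comparison.

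Neither part changes the co-primary inference. The change is worth making, but the trial's main conclusions do not depend on it.

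**What to change.** In SAP C:
- Say which outcomes the subgroups apply to. For each factor and each co-primary, report the within-level estimates with 95% CIs and one treatment-by-factor interaction (homogeneity) estimate and test, exact or penalised where events are few.
- Base any statement that the effect differs on the interaction, not on significance within levels.
- Label the interaction tests exploratory and unadjusted, with a note that at least one nominal result in eight is expected by chance in about 30% of trials.
- Flag biliary stent placement as a post-randomisation factor.
- State that only the two co-primaries are confirmatory, and that secondary and safety outcomes are reported as estimates with 95% CIs.

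In SAP D, add the interaction result to the forest plot.

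The cost is SAP wording and 16 simple tests, with no change to design or sample size. The SAP dictionary lists no variable for study site or papilla status, so those two would have to be added for the planned subgroups in any case. The downside is small: nominally significant subgroup or secondary results could not be presented as findings.

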## **9. Statistical Considerations**

### **9.1. Hypothesis and Sample Size Calculations**

The first co-primary outcome considers technical success of the ERCP procedure. Overall technical success rates in ERCP vary widely depending on the definitions employed. It is widely agreed upon that a cannulation rate greater than 90% (in native papillae) is an attainable key performance indicator (KPI) in ERCP performed for choledocholithiasis. However, in cases of malignant biliary obstruction, especially at low-volume centers, cannulation rates appear to be significantly lower. When one considers overall procedural success rate, these targets become even less clear, with studies reporting between 60 and 90% success rates depending on the definitions employed.

Prospective data from our center have been analyzed to assess our group's rates, based on 10 months of procedures in over 600 patients having undergone ERCP. Deep cannulation rates in native papillae at our center are approximately 96%. Overall procedural success in all-comers is approximately 92%, with 4% representing cannulation failures, 4% representing inability to clear or relieve obstruction in the duct(s) of interest.

Thus, when comparing clinical efficacy between DEC and traditional duodenoscopes, we selected an overall baseline technical success rate of 92% based on our experience. We propose that technical success of DEC within a margin of 7% of traditional duodenoscopes will result in an ability to conclude non-inferiority of DEC. A hypothesis will therefore be tested that the overall technical success rate with DEC will be at least 85%:

$$H_0: P_{CON} \geq P_{DEC} + d \text{ (Inferior)} \quad H_1: P_{CON} - d < P_{DEC} \text{ (Non-inferior)}$$

where  $P_{DEC}$  is the overall technical success rate for DEC in this study,  $P_{CON}$  is the overall technical success rate for traditionally designed duodenoscopes (control),  $d$  is the set non-inferiority limit of 7%, and  $H_0$  and  $H_1$  are the null and alternate hypotheses, respectively.

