An exact test will be used to test the one-sided hypothesis that DEC is non-inferior to control duodenoscopes. Using a power of 80% with a one-sided alpha of 0.025, 236 subjects in each arm will be required, for a total of 472 patients. To compensate for possible loss of subjects due to attrition, an additional 10% of subjects will be enrolled, for a **total of 520 subjects**. It is therefore estimated that the study will require **9-12 months to complete**, based on the estimated volume of ERCPs and study enrolment rates at our center. No interim analyses will be planned.

The second co-primary outcome considers persistent bacterial contamination rate of the duodenoscopes after ERCP. A recent nation-wide analysis showed a persistent bacterial contamination rate of 22% after standard disinfection and reprocessing of duodenoscopes. This was common across multiple duodenoscope manufacturers and models. In particular, the Pentax ED34-i10T duodenoscope demonstrated a persistent contamination rate of 27%, though there was a small sample size of 11 assessing this group. No other published studies have reported specifically on reprocessing of ED34-i10T. However, real-world data from the FDA demonstrate a 9.3% total sample positivity rate among Pentax duodenoscopes. Furthermore, our preliminary data based on post-reprocessing bioluminescence scans demonstrate that 10% of ED34-i10T duodenoscopes require repeat re-processing due to counts representative of residual contamination.

Thus, when comparing persistent contamination between DEC and traditional duodenoscopes, we set an overall expected persistent contamination rate of 10% in the control arm. We propose that reduction in persistent bacterial contamination from 10% with ED34-i10T to 3% with DEC (a relative risk reduction of 67%) would be considered clinically significant. A hypothesis will therefore be tested that the persistent bacterial colonization rate with DEC will be 3% or lower:

$$H_0: P_{DEC} \geq P_{CON} \text{ (Equivalent or Inferior)} \quad H_1: P_{DEC} < P_{CON} \text{ (Superior)}$$

where  $P_{DEC}$  is the persistent contamination rate for DEC in this study,  $P_{CON}$  is the persistent contamination rate for traditionally designed duodenoscopes (control), and  $H_0$  and  $H_1$  are the null and alternate hypotheses, respectively.

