| charlson         | Charlson comorbidity index                                                      | (whole number scale from 0 to 33)                                                                                                                                                                                                                                                                     |
| disposition      | patient disposition                                                             | 0 = outpatient; 1 = inpatient                                                                                                                                                                                                                                                                         |
| trainee          | trainee participation in ERCP                                                   | 0 = no trainee; 1 = trainee present                                                                                                                                                                                                                                                                   |
| indication       | indication for ERCP                                                             | 1 = ampullary obstruction or stricture; 2 = bile leak; 3 = benign or anastomotic biliary stricture; 4 = suspected or confirmed malignant biliary obstruction; 5 = cholangitis; 6 = suspected or confirmed biliary stones; 7 = repeat planned procedure including stent removal or exchange; 8 = other |
| complexity       | procedural complexity as defined by ASGE grade for complexity of ERCP           | 1 = Grade I; 2 = Grade II; 3 = Grade III; 4 = Grade IV                                                                                                                                                                                                                                                |
| ercp_prev        | previous ERCP                                                                   | 0 = no; 1 = yes                                                                                                                                                                                                                                                                                       |

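### Technical success is compared without covariate adjustment although prognostic baseline data are already recorded: a small, cheap gain in precision is missed, but the planned analysis is valid

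*Supplement*

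**What the plan says.** SAP section C (Analysis) sets one rule for all outcomes: "Outcomes will be compared between groups in an intention-to-treat analysis without adjustment". Proportions are compared by two-tailed Fisher's exact and chi-squared tests and reported as relative risks and numbers needed to treat. Papilla status, indication, inpatient status and age appear there only as post hoc subgroup factors.

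The SAP data dictionary (section B) holds age, disposition (outpatient or inpatient), indication in eight categories including suspected or confirmed malignant biliary obstruction, and "previous ERCP". Arms are coded as scope design A or B.

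The latest protocol version (section 5.4) randomises 1:1 in permuted blocks of 8 and states no stratification factor. Section 9.1 sizes technical success as a non-inferiority comparison: "we selected an overall baseline technical success rate of 92% based on our experience", an absolute margin of 7 points, "Using a power of 80% with a one-sided alpha of 0.025", and "236 subjects in each arm will be required, for a total of 472 patients". It specifies an exact test.

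On prognosis, section 9.1 notes that "in cases of malignant biliary obstruction, especially at low-volume centers, cannulation rates appear to be significantly lower". Section 7.1.1 makes the criterion for success depend on the indication.

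**The concern.** The non-inferiority claim rests on the width of an interval around a difference expected to be near zero. The trial admits patients with any indication for ERCP, so case mix runs from stent removal to malignant obstruction. Without stratification or adjustment, chance differences in case mix between arms stay in the estimate as noise.

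A risk difference standardised over baseline covariates targets the same marginal quantity as the 7-point margin. In large samples its standard error is usually a little smaller when the covariates predict outcome. The data needed are already in the SAP dataset. At stake is a little precision against the margin, and protection against a visible imbalance that could not credibly be handled once the arms are known.

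**Working it through.** **1. Reproduce the plan's figure.** Inputs from protocol section 9.1: control success 0.92, margin 0.07, one-sided alpha 0.025, power 80%. Success with DEC under the alternative is not stated; I take it as 0.92.

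n per arm = 2 × 0.92 × 0.08 × (1.960 + 0.842)² / 0.07² = 235.8, so 236 per arm and 472 in total. This matches the protocol. The formula is that of an unadjusted risk difference, so the unadjusted analysis has the power it was planned to have.

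**2. Power at the SAP's analysed number.** SAP section A gives 518 for the technical outcome, about 259 per arm.

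- SE = √(2 × 0.92 × 0.08 / 259) = 2.384 points
- 95% CI half-width = 1.96 × 2.384 = 4.67 points
- Power = Φ(7 / 2.384 − 1.96) = 83.6%

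**3. Effect of adjustment.** If baseline covariates explain a share R² of outcome variance, the variance of the risk difference is multiplied by about (1 − R²). R² is not in the documents, so each value below is an assumption.

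| Assumed R² | Power, 259 per arm | CI half-width (points) |
|---|---|---|
| 0 | 83.6% | 4.67 |
| 0.02 | 84.3% | 4.63 |
| 0.05 | 85.4% | 4.55 |
| 0.07 | 86.1% | 4.51 |
| 0.10 | 87.2% | 4.43 |

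**4. What R² is plausible?** For one binary covariate, R² = prevalence × (1 − prevalence) × gap² / (0.92 × 0.08). Take malignancy at an assumed prevalence of 25%:

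- gap of 5 points: R² = 0.25 × 0.75 × 0.05² / 0.0736 = 0.006
- gap of 10 points: 0.025
- gap of 15 points: 0.057
- gap of 20 points: 0.102

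Only the widest gap takes R² above 0.07.

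**5. Simulation of the estimator.** N = 518, 92% success in both arms, with assumed prevalences of 60% native papilla, 30% malignant or complex indication and 35% inpatient. The unadjusted Wald risk difference was compared with logistic standardisation using an influence-function SE (8,000 trials per row).

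| Assumed failure odds ratios (native / indication / inpatient) | R² | Variance ratio, adjusted to unadjusted | Power, unadjusted to adjusted |
|---|---|---|---|
| 2 / 2 / 1.3 | 0.02 | 0.99 | 83.6% to 84.5% |
| 4 / 2.5 / 1.5 | 0.04 | 0.97 | 83.2% to 84.5% |
| 8 / 3 / 1.5 | 0.07 | 0.94 | 83.6% to 86.3% |

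Type I error at the margin was 2.4–2.6% adjusted and 2.5–2.7% unadjusted. With covariates that predict nothing (6,000 trials), the variance ratio was 1.006 and power went from 83.5% to 83.8%, so a few tenths of a point in any row may be an artefact of the standard error.

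**6. Check against the protocol's own rates.** Section 9.1 reports about 96% deep cannulation in native papillae, so about 4% failure. It also gives 4% cannulation failures among all-comers, plus 4% failures to clear or relieve obstruction. No papilla gradient in cannulation is visible. Suppose 60% are native, non-native failure is 4%, and all remaining failures fall on native cases. Native failure is then (8 − 0.4 × 4) / 0.6 = 10.7%, and the odds ratio is (0.107 / 0.893) / (0.04 / 0.96) ≈ 2.9. On that reading the papilla odds ratios of 4 and 8 are too strong, and the first row of the simulation is the closest fit.

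**The case against.** The strongest objection is that nothing is broken. The sample size was computed for an unadjusted comparison, no stratification factor calls for adjustment, and the unadjusted interval already allows for chance imbalance. All of that stands.

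A reader might infer that the protocol itself names papilla status, indication, inpatient status and age as drivers of ERCP success. It does not. The malignancy sentence concerns cannulation, especially at low-volume centres, and both sites are described as high-volume. Native papillae are mentioned only to define the population of a cannulation figure. Section 9.1 attributes variation in overall success to the definitions used, and nothing there makes inpatient status or age prognostic. The tailored criteria may also flatten the gradient: for difficult stones, stenting with a plan to clear the duct later counts as success.

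Part of this can be answered. Cannulation failures are half of the expected 8% failures, so a factor that affects cannulation bears on the endpoint. Section 7.1.1 also ties the success criterion to indication. That makes some prognostic value for indication reasonable, but it gives no size.

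Two practical objections stand. Previous ERCP is not papilla status: the SAP defines papilla status as native or prior sphincterotomy, and no such variable is in its dictionary. And the protocol specifies an exact test, which a standardised risk difference is not, so more than SAP wording is affected.

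**Conclusion.** The point holds as a minor efficiency suggestion. The SAP leaves unused baseline information that is already recorded, and adjustment would probably narrow the interval slightly. Under assumed R² of about 0.02 to 0.07, the gain at 518 analysed is about 0 to 3 power points and less than 0.2 points of CI half-width from 4.67. The protocol's own cannulation figures favour the lower end for papilla status.

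The documents do not support a stronger reading, that the unadjusted analysis is biased, invalid or underpowered: 236 per arm reproduces exactly, and 518 gives about 83.6%. All sizes rest on equal true success of 92% in both arms and on covariate strengths and prevalences that the documents do not give.

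**What to change.** While the arms are still coded A and B, amend SAP section C for technical success only:

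- **Primary estimate:** risk difference standardised from a logistic model with arm, malignant versus other indication, previous ERCP (labelled as a proxy for papilla status), inpatient status and age. Give a 95% CI by influence function or bootstrap and compare it with the 7-point margin.
- **Covariates:** use only values known before randomisation, and fix the list in advance. Exclude biliary stent placement, which occurs after randomisation, and procedural complexity, which may reflect what was done during the procedure.
- **Sensitivity analysis:** keep the unadjusted exact non-inferiority test of protocol section 9.1, report it, and state that it is no longer the primary test.

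**Cost:** SAP wording, a few lines of R, and a matching change to the protocol's exact-test wording. No new patients or data are needed.

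**Downside:** the method is asymptotic, and only about 41 failures are expected (0.08 × 518 = 41.4), so the covariate list must stay short. If the sponsor prefers to keep the exact test as primary, the adjusted estimate could be pre-specified as supportive, and little would be lost.

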### **5.4. Randomization and Allocation**

Patients fulfilling the inclusion/exclusion criteria above will be randomized following consent in a 1:1 ratio. Permuted block randomization will be utilized in blocks of 8 patients. Allocation will be to one of two groups: 1) ERCP using ED34-i10T2 duodenoscope with DEC or 2) ERCP using a conventional duodenoscope (ED34-i10T). Confidential random number allocation will be accessed via a secure internet software. The study investigators, outcome adjudicators and patients will be blinded to allocation. The endoscopist will not be blinded. In cases where additional or alternate duodenoscope(s) is/are required to achieve the desired goal of the ERCP procedure, the choice(s) of device(s) will be left to the discretion of the endoscopist, regardless of the study arm to which the patient has been allocated.

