**A) Data groups:**

1. MICROBIOLOGY OUTCOME – co-primary outcome 1 (superiority outcome). N = 422 patients.
2. TECHNICAL OUTCOME – co-primary outcome 2 (non-inferiority outcome). N = 518 patients.
3. SAFETY OUTCOMES AND SECONDARY OUTCOMES. N = 518 patients.

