**B) Variables and data dictionary:**

| Variable Name | Description/ Definition                                            | Coding                             |
|-----------------------------|----------------------------------------------------------------------------------|--------------------------------------------------|
| study_id                    | unique study identifier                                                          | (whole number)                                   |
| scope_random                | study randomization and allocation                                               | 1 = scope design A; 2 = scope design B (blinded) |
| tech_outcome                | technical success, co-primary outcome #1 (non-inferiority)                       | 0 = unsuccessful; 1 = successful                 |
| micro_outcome               | persistent microbial contamination, co-primary outcome #2 (superiority)          | 0 = no event; 1 = event                          |
| ae_pancreatitis             | pancreatitis following ERCP (ascertained at 30-day follow-up)                    | 0 = no event; 1 = event                          |
| ae_bleeding                 | bleeding following ERCP (ascertained at 30-day follow-up)                        | 0 = no event; 1 = event                          |
| ae_perforation              | perforation following ERCP (ascertained at 30-day follow-up)                     | 0 = no event; 1 = event                          |
| ae_cholang                  | cholangitis following ERCP (ascertained at 30-day follow-up)                     | 0 = no event; 1 = event                          |
| ae_cardio_resp              | cardiorespiratory adverse event following ERCP (ascertained at 30-day follow-up) | 0 = no event; 1 = event                          |
| ae_death                    | death following ERCP (ascertained at 30-day follow-up)                           | 0 = no event; 1 = event                          |
| ice_duo_num                 | duodenoscope number                                                              | (one of several pre-specified numbers)           |
| ice_duo_ease_md             | ease of use of overall scope design, according to endoscopist/trainee            | (scale from 0 to 10)                             |

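### The SAP gives absolute effects a 95% CI only through the NNT, which has no ordinary interval when the arms are similar; plan a risk-difference CI for every binary outcome.

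*Supplement*

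**What the plan says.** SAP section C holds the whole analysis plan. It names the tests ("Two-tailed Fisher's exact tests and chi-squared tests will be used to compare proportions") and the analysis set ("Outcomes will be compared between groups in an intention-to-treat analysis without adjustment"), then the effect measures: "Comparisons will be reported using relative risks (RRs) and numbers needed to treat (NNTs) along with their respective 95% confidence intervals (CIs". The sentence is not limited to particular outcomes. It gives no method for the NNT interval, no rule for a difference compatible with zero, and no rule for an arm without events.

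SAP section D lists the output "Summary of RRs, ARRs, RRRs, NNTs, NNHs". The absolute risk reduction (ARR) will therefore be tabulated, but neither section promises it an interval.

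Section A gives the sizes: "SAFETY OUTCOMES AND SECONDARY OUTCOMES. N = 518 patients", and for microbiology "co-primary outcome 1 (superiority outcome). N = 422 patients". The data dictionary in section B codes the harms as binary, for example "pancreatitis following ERCP (ascertained at 30-day follow-up", and includes perforation and death.

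Section 9.1 of the latest protocol covers only the two co-primary hypotheses and their sample sizes. It sets the non-inferiority margin for technical success as an absolute difference of 7%.

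**The concern.** The NNT is the reciprocal of the risk difference, and a reciprocal breaks at zero. If the data are compatible with no difference, the set of compatible NNTs runs from some number needed to treat for benefit, through infinity, to some number needed to harm. That set cannot be printed as a lower and an upper limit. An analyst who inverts the two risk-difference limits and prints them as a range gets one that leaves out the point estimate.

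This matters most for harms and for technical success, where similar arms are the hoped-for result. Readers there want to know how large an absolute excess the data still allow. The SAP gives that information an interval only through the NNT, the one absolute measure that fails when the arms are similar.

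**Working it through.** **Inputs.** Safety and technical N = 518 and microbiology N = 422 (SAP section A). Allocation: "will be randomized following consent in a 1:1 ratio" (protocol section 5.4). I assume even splits, so 259 and 211 per arm. Control technical success 92%, margin 7%, contamination 10% v 3% (protocol section 9.1). The documents give no adverse event rates, so all event counts and harm rates below are assumptions.

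**1. The plan's own figures.** Non-inferiority with equal true rates of 92%:

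n = (1.960 + 0.842)² × 2 × 0.92 × 0.08 / 0.07² = 7.85 × 0.1472 / 0.0049 ≈ 236 per arm, as stated.

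So the design assumes no true difference in technical success. The 194 per arm for 10% v 3% also reproduces (pooled variance, no continuity correction). The documents contain no NNT or NNT interval to reproduce.

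**2. Why inversion fails.** Let d be the risk difference with limits L < 0 < U. If d > 0, then d < U gives 1/d > 1/U, so 1/d lies above both 1/U and 1/L. If d < 0, then 1/d lies below both. The estimate is therefore always outside the range from 1/L to 1/U. If d = 0, the NNT is infinite.

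**3. Example with assumed counts, 26/259 v 22/259.**
- Risks 10.04% and 8.49%; d = 1.54 points; 1/d = 65.
- Wilson limits: 6.94% to 14.30% and 5.68% to 12.53%.
- Newcombe lower limit: 1.54 - √(3.10² + 4.03²) = -3.54 points.
- Newcombe upper limit: 1.54 + √(4.26² + 2.82²) = 6.66 points (before rounding).
- Inverted limits: 1/(-0.0354) = -28 and 1/0.0666 = 15. The range -28 to 15 excludes 65. The valid statement is 15 or more in the direction of the estimate, through infinity, to 28 or more in the other direction.
- RR = 26/22 = 1.18. SE of log RR = √(1/26 - 1/259 + 1/22 - 1/259) = 0.276, giving 0.69 to 2.03, an ordinary interval.

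**4. How often the risk-difference CI includes zero** (exact binomial enumeration):

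| True rates | Per arm | CI type | Includes zero |
|---|---|---|---|
| 92% v 92% | 259 | Newcombe | 95.3% |
| 5% v 5% | 259 | Newcombe | 95.3% |
| 10% v 10% | 259 | Newcombe | 95.1% |
| 5% v 8% | 259 | Newcombe | 73.0% |
| 10% v 3% (microbiology design) | 211 | Wald | 14% |

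Microbiology near its design rates, 21/211 v 6/211, gives NNT 14 with Wald-based limits 8.5 to 40, an ordinary interval. Technical failures of 21 v 19 in 259 (assumed) give NNT 130 with Wald-based inverted limits of -26 and 19.

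**5. Rare harms.** With q = (1 - p)^259, P(at least one empty arm) = 1 - (1 - q)² and P(both empty) = q².

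| Assumed rate p | At least one arm empty | Both empty |
|---|---|---|
| 0.3% | 71% | 21% |
| 0.5% | 47% | 7.5% |
| 1% | 14% | 0.5% |

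With one empty arm the RR is 0 or infinite, but a score interval keeps one finite limit: for 0 v 3 of 259 the upper limit is about 1.27. The risk difference for 3 v 0 is +1.2 points (Newcombe -0.5 to 3.3).

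**The case against.** A reader might infer that most safety results would carry meaningless error bars. The documents do not support that, for four reasons.

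- The same sentence plans a 95% CI for the RR, which is valid whenever both arms have events. The output list also includes a table of proportions by arm, from which the absolute difference and its interval can be recovered.
- The SAP does not say that NNT limits will be formed by plain inversion. It lists both NNTs and NNHs, so the correct benefit-infinity-harm form is open to a careful analyst. The gap is an unspecified method, not a prescribed error.
- Not every outcome is touched. Procedure time, disinfection and reprocessing times and the ease-of-use scale take no NNT, and microbiology at its design rates is usually safe.
- The 95% figure is close to the definition of a 95% CI under no difference, and how many harms are affected depends on rates the documents do not give. Nor is the RR undefined whenever an arm is empty; that needs both arms empty.

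All of this stands, and it limits the point to the absolute scale. It does not close the gap. Nothing in the SAP tells the analyst what to do when the difference is compatible with zero, and no risk-difference interval is planned.

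**Conclusion.** The point holds as a reporting gap of moderate weight. For any binary outcome whose risk-difference CI includes zero, the planned NNT has no ordinary 95% interval, and plain inversion gives limits that exclude the estimate. With equal true rates at 259 per arm this happens in about 95% of trials. Technical success would normally be affected, because its sample size rests on equal rates. How many harms are affected rests on assumed event rates and on an even split.

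No test, sample size or error rate changes. What is missing is a usable absolute-scale interval. The 7% margin calls for that same interval, because it too is an absolute difference.

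**What to change.** In SAP section C, replace the sentence on effect measures with wording such as: each binary outcome will be reported as the risk difference with a Miettinen-Nurminen (or Newcombe) 95% CI, alongside the RR with its 95% CI; an NNT or NNH with its CI will be given only where the risk-difference CI excludes zero, and otherwise will be omitted or shown in the benefit-infinity-harm form.

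Add a rule for sparse outcomes. Where one arm has no events, rely on the risk-difference CI and give the RR only with a score-type or one-sided limit. Where both arms have none, give no RR.

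Name one of the two interval methods, and add the risk-difference CI to the second output in section D.

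The cost is SAP wording and a standard R function, with no new data. The downside is that fewer NNTs will be printed.
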